### Eligibility Criteria

The registry population will be comprised of critically ill patients, including children who undergo treatment with the CytoSorb device as part of their routine clinical care. To best represent real-world practice and avoid selection bias, participating sites will ideally include all patients receiving the CytoSorb device consecutively, without preselection (Textbox 2).

Inclusion and exclusion criteria.
**Inclusion criteria**
CytoSorb device utilizationInformed consent for prospective registry participation
**Exclusion criteria**
Use of CytoSorb device for antithrombotic drug removal onlyIntraoperative use of CytoSorb device during cardiac surgery only

### Ethical Considerations

This registry is being conducted in accordance with International Organization for Standardization (ISO) 14155:2020; the Declaration of Helsinki; the standards of Good Clinical Practice, as defined in the International Conference on Harmonization E6 Guideline for Good Clinical Practice; as well as all other local legal requirements. Prior to initiation of the registry, IRB and IEC approval must be received for the protocol, sample informed consent form (ICF), and any other documents that pertain to patient information and recruitment methods such as advertisements. All subsequent protocol amendments and changes to the ICF must also be submitted and approved by the IRB and IEC. The initial international ethics approval at Vall D’Hebron University Hospital, Barcelona, Spain, is PR(AG)86/2022. Each center must obtain approval from its responsible IRB before activation.

To collect in-hospital and postdischarge data, the investigator or designee must obtain a signed, IRB- and IEC-approved ICF from patients or their legally authorized patient representatives when the patient is identified as a potential candidate for the registry (refer to Multimedia Appendix 1 for the ICF). Consent is obtained either from the patient or, according to standard procedures in emergency situations, via the legally authorized patient representative. The ICF contains all the elements required by ISO14155:2020 and only includes data collection, as the indication of treatment with CytoSorb itself is solely at the discretion of the treating physician. In cases where patients are unable to give consent, a declaration of consent must be obtained from a legal representative, taking into account the patient’s presumed willingness. The legal representative may be an authorized representative appointed by a power of attorney or a court-appointed caregiver (health care task group) according to local regulations. For children, dedicated ICFs are provided. Patients who are not able to give their consent initially but who become able to during their stay in hospital will be informed about the registry when they are able again to consent, and then the written informed consent on participation in the registry is obtained. Any patient has the right to withdraw from the registry at any time without penalty or loss of benefit. There is no direct financial compensation for participants.

For each enrolled participant, an electronic case report form (eCRF) will be maintained. All clinical data will be extracted from medical records by the site investigator(s) and their designees. Data accuracy will be verified by centralized monitoring. Data will be entered in a deidentified manner; that is, patients who consented will be assigned a consecutive patient identification only traceable by the site. The eCRF will be available for inspection by the sponsor and its designees before, during, and upon completion of the registry. Patient rights regarding information, correction, deletion, and general handling of data will be respected according to the European General Data Protection Regulation. A full data readout is performed at least annually. The data are treated confidentially at all times and are protected against unauthorized access. In the event of premature termination of the registry, no further data will be collected. Transmission of registry-related data, for example, for statistical analysis, to countries with a level of data protection that may differ from that of the European Union, such as the United States, takes place exclusively in deidentified form. This ensures data confidentiality, as data cannot be assigned to a specific or identifiable actual person. Publication of the results of the registry study will be in anonymous form only.

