### Data Capture and Outcomes

As per the registry protocol, there are no prespecified assessments or medical treatments to be performed other than a follow-up telephone call at 90 days (plus an additional 20 days if needed for administerial reasons) after the start of CytoSorb treatment. Data collection is performed based on medical chart review and transcription of deidentified data collected from hospital admission through discharge. The following key parameters are included (Textbox 3).

Data from the following time points will be collected if available (Textbox 4).

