### Analysis and Statistical Methods

Descriptive statistics and patient data listings will be used to summarize the data. Continuous variables will be summarized by nonmissing values (n), mean and SD (in case of normal distribution), median, 25th and 75th percentiles (in case of nonnormal distribution), and minimum and maximum. Categorical variables will be summarized by frequencies and percentages. Stratification of descriptive categories within treatment groups may occur if such elaborations are thought to be useful. Inferential statistical tests may be used, as appropriate, with an α critical value of .05 to indicate statistical significance. Inferential statistical tests will be 2-sided, unless specified otherwise. Also, 95% CIs may be used to compare event rates to a historical and clinically meaningful standard or to investigate the course of biomarkers (or certain laboratory values) after CytoSorb therapy. Multivariate analysis may be used to determine independent predictors of study outcomes. Missing data is unavoidable for critically ill patients treated in the intensive care unit (ICU). The principle of analyses is to only include the nonmissing observations. For inflammatory biomarkers or laboratory values that are highly associated with the use of hemoadsorption devices, sensitivity analyses will be performed by applying a multiple imputation method under the missing-at-random assumption.

Unless specified otherwise, minimum and maximum will be displayed to the same level of precision as the observed value. Mean and median will be displayed to 1 level of precision greater than the observed value. The SD and SE will be displayed to 2 levels of precision greater than the observed value. All *P* values will be rounded to and displayed as 3 decimals. If a *P* value less than .001 occurs, it will be shown in tables as <.001.

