## Results

The COSMOS registry is an international registry executed in countries where the device is approved and routinely used in everyday clinical practice. It started with the inclusion of the first patient on July 15, 2022. There is no prespecified sample size for the registry, but the current estimation is that with annual enrollment of approximately 300 patients, the registry can reach up to 3000 patients in 10 years. The COSMOS registry is now actively enrolling in 4 countries (Germany, Spain, Portugal, and Italy), with plans to expand to other countries outside of Europe. As of August 1, 2024, a total of 199 patients are included in the registry.

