### Conclusions

The intent of the COSMOS registry is to inform data-driven optimization of CytoSorb therapy across a broad variety of indications and to provide important safety information fulfilling regulatory requirements on postmarket surveillance. Furthermore, the current design of the COSMOS registry allows the potential for future registry-embedded RCTs [69] to answer specific prespecified hypotheses, a process that will require separate protocols, consent, and ethics approval.

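### Ending all data collection at premature termination would leave already enrolled patients without their planned day-90 vital status and cause of death

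*Protocol article*

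**What the plan says.** The rule stands in the protocol article under Ethical Considerations, among the sentences on data handling: "In the event of premature termination of the registry, no further data will be collected". The text does not separate the end of enrolment from the end of follow-up.

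Other parts of the article bear on it:

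- **Follow-up.** Data Capture and Outcomes plans "a follow-up telephone call at 90 days (plus an additional 20 days if needed for administerial reasons) after the start of CytoSorb treatment". Textbox 3 lists 90-day mortality and cause of death. It separately lists ICU and in-hospital mortality, and a study-exit item made up of vital status and exit date.
- **Reasons to stop.** Textbox 1 (Study Setting) includes previously unknown device-safety problems, recruitment difficulties and a decision by the sponsor.
- **Purpose.** The Objectives section makes the registry part of postmarket clinical follow-up. The Conclusions say that it is meant "to provide important safety information fulfilling regulatory requirements on postmarket surveillance".
- **Missing data.** Analysis and Statistical Methods says: "The principle of analyses is to only include the nonmissing observations". Its one stated exception does not name mortality: "For inflammatory biomarkers or laboratory values that are highly associated with the use of hemoadsorption devices, sensitivity analyses will be performed" by multiple imputation.
- **Device events.** Data Capture and Outcomes has the sponsor analyse serious device events at once, and keeps the statutory reporting duties.

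**The concern.** Day-90 vital status and cause of death are the longest-term outcomes in the registry, and the day-90 call is the only assessment that the protocol itself adds to routine care. Taken at its word, the termination rule cancels that call for every patient still waiting for it, and also ends the chart review of patients still in hospital. If the registry stops because of a new safety problem, the most recently treated patients would be the ones whose outcome is not followed to day 90.

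There may also be an effect on the estimate. A death before the stop settles a patient's 90-day status. A patient alive at the stop has none. If such survivors are treated as missing and left out while the early deaths stay in, reported 90-day mortality rises. The article foresees comparing event rates with a historical standard, and a one-sided shift would matter there.

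**Working it through.** **Inputs from the article (Results).** "It started with the inclusion of the first patient on July 15, 2022". "As of August 1, 2024, a total of 199 patients are included in the registry". The projection is that "with annual enrollment of approximately 300 patients, the registry can reach up to 3000 patients in 10 years". Follow-up runs to day 90, or to day 110 with the call allowance.

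**The plan's own figure.** 300 × 10 = 3000, which reproduces.

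**Observed accrual.** July 15, 2022 to August 1, 2024 is 748 days. 199 / 748 × 365.25 = 97.2 per year.

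**Patients inside the window at a stop**, k = rate × window / 365.25:

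- At 97.2 per year: 97.2 × 90 / 365.25 = 23.9, and 97.2 × 110 / 365.25 = 29.3. These are 12% and 15% of 199.
- At 300 per year: 73.9 and 90.3.

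**How many of these would lack a status.** The article gives no mortality or time to death, so both are assumptions: 90-day mortality of 45%, exponential time to death with a mean of 20 days among those who die, uniform accrual, and every death before the stop known. Under this curve e^-4.5 = 1.1% of the deaths fall after day 90, and this is ignored. The average share of patients in a window W who have already died is

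f = 0.45 × [1 − (20/W)(1 − e^(−W/20))]

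- W = 90: f = 0.351, so 23.9 × 0.649 = 15.5, about 16 patients. At 300 per year, 73.9 × 0.649 = 48.
- W = 110: f = 0.369, so 29.3 × 0.631 = 18.5, about 18 patients (18.48 before rounding). At 300 per year, 90.3 × 0.631 = 57.

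So about 16 to 18 patients, 8% to 9% of 199, would have no day-90 status.

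**Effect on 90-day mortality, if early deaths count and survivors drop out.** With true mortality m and N enrolled, the reported value is

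[(N − k)m + k f] / [(N − k) + k f]

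Example with N = 199, k = 23.9, m = 0.45, f = 0.351: (175.1 × 0.45 + 8.4) / (175.1 + 8.4) = 87.2 / 183.5 = 47.5%, which is 2.5 points too high.

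Range over assumed mortality of 30% to 60% and death-time constants of 10, 20 and 40 days (death times scaled to fall within 90 days):

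| Enrolled at the stop | Rate per year | 90-day window | 110-day window |
|---|---|---|---|
| 199 | 97 | +1.9 to +2.9 points | +2.6 to +3.6 points |
| 600 | 300 | +1.9 to +2.9 | +2.6 to +3.7 |
| 1500 | 300 | +0.7 to +1.1 | +1.0 to +1.4 |
| 3000 | 300 | +0.4 to +0.6 | +0.5 to +0.7 |

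The shift is upward in every scenario. It is zero if the analysis is limited to patients treated at least 90 days (110 with the call allowance) before the stop, and largely avoided if patients are censored at the stop.

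**The case against.** The sentence sits in a paragraph on confidentiality and may be meant as an assurance to participants. The article is condensed, and close-out steps could stand in the full protocol. Part of this is fair: the intention may well be privacy. But the article states a rule without exception and gives no reason for it, so the point rests on what is written and not on an omission.

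Four stronger readings are tempting, and the documents do not support them:

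- **That 90-day mortality will be biased.** The article fixes no estimator for 90-day mortality, and the analysis plan, which is not shown, may choose one that avoids the problem. The study-exit vital status and date would support censoring. Even where the bias arises it is modest: 2.5 points at 199 patients compares with a 95% half-width of 1.96 × √(0.45 × 0.55 / 199) = 6.9 points.
- **That all 24 to 29 patients would lack a status.** Those who died before the stop have a known one. The missing group is nearer 16 to 18 under the stated assumptions.
- **That safety follow-up ends.** Root-cause analysis of serious device events and statutory reporting continue. These cover recognised device events, however, not vital status and cause of death in every treated patient.
- **That existing consent already permits the calls.** Consent covers in-hospital and postdischarge data, but the consent form is not shown, and whether it reaches past termination cannot be checked.

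**Conclusion.** The point holds as a conflict between the termination rule and both the planned day-90 follow-up and the postmarket safety purpose. What would be lost is day-90 vital status and cause of death for about 16 to 18 patients at present accrual, or 48 to 57 at 300 per year, assuming 45% mortality and a mean of 20 days to death. Discharge data of patients still in hospital would be lost as well. No analysis plan can restore these.

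The upward bias in 90-day mortality is a secondary and conditional matter: about 2 to 4 points at 199 patients and under 1 point near 3000, only if early deaths in incomplete windows are kept and survivors are dropped. The whole concern depends on a premature stop, which may never happen. The loss would be permanent, however, and is cheap to prevent now, so the sentence should be changed.

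**What to change.** Replace the sentence with a rule that on premature termination enrolment stops, while discharge data and the day-90 (+20) call are completed for patients already enrolled. The exceptions are withdrawal of consent and a prohibition by an authority or ethics committee. Check first that the consent wording allows collection after termination, and amend it if it does not.

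For the case where collection must stop, state that vital status and the registry exit date are used to censor patients at the stop, and that 90-day mortality is estimated by Kaplan-Meier from the first CytoSorb start. This needs vital status to be confirmed as of the exit date, because a death after discharge may otherwise go unnoticed without the call.

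The cost is a protocol amendment with ethics submission, possibly a change to the consent form, and up to about 110 days of calls that are already planned. The fallback removes most of the bias but does not recover the lost outcomes.

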### Data Capture and Outcomes

As per the registry protocol, there are no prespecified assessments or medical treatments to be performed other than a follow-up telephone call at 90 days (plus an additional 20 days if needed for administerial reasons) after the start of CytoSorb treatment. Data collection is performed based on medical chart review and transcription of deidentified data collected from hospital admission through discharge. The following key parameters are included (Textbox 3).

Data from the following time points will be collected if available (Textbox 4).

Key parameters.DemographicsBaseline characteristics including Acute Physiology And Chronic Health Evaluation II score, respective Pediatric Index of Mortality-3 score for children, and Charlson Comorbidity Index scoreIndication for CytoSorb treatmentDetails on the extracorporeal circuit used (eg, type of platform, blood flow rate, and anticoagulation regimen), integration of CytoSorb, and duration of treatmentChanges in Sequential Organ Failure Assessment scores or subscores and Pediatric Logistic Organ Dysfunction-2 score for childrenChanges in inflammatory biomarkers (C-reactive protein, procalcitonin, leukocytes, interleukin-6, and other interleukins)Laboratory results from hematology, chemistry, coagulation, and arterial blood gas analysis as well as additional drug level measurementsDuration of organ support therapies (number of days on extracorporeal membrane oxygenation or extracorporeal life support system, number of days on continuous renal replacement therapy, number of days on mechanical ventilation, and number of days on concomitant procedures like therapeutic plasma exchange)Daily fluid balanceVasopressor requirements (type, dose, and duration)Ventilation parametersLiver disease assessment (eg, hepatic encephalopathy, bilirubin, bile acids, model for end-stage liver disease score, respective pediatric end-stage liver disease score for children, European Association for the Study of Liver—Chronic Liver Failure score, Maddrey score, and Lille score)Acute kidney injury assessment, including Kidney Disease Improving Global Outcomes severity score and myoglobin and creatine kinase levels for rhabdomyolysisCritical illness polyneuropathyCumulative blood productsConcomitant therapies including plasmapheresis and medicationLength of intensive care unit (ICU) and hospital stayICU and in-hospital mortalitySafety performance of CytoSorb device, including collection of any unexpected serious adverse device effectsCases of device deficiencyLong-term follow-up on day 90 (+20) including 90-day mortality and cause of deathStudy exit: vital status and registry exit date

Data collected.Baseline (at intensive care unit [ICU] admission)Before start of CytoSorb therapy (maximum 24 hours prior)During CytoSorb therapyAfter CytoSorb therapy (maximum 24 hours afterward)At discharge from ICUAt discharge from hospitalFollow-up on day 90 (+20)

A device deficiency is defined as any inadequacy of a medical device with respect to its identity, quality, durability, reliability, usability, safety, or performance, including malfunctions, use errors, and inadequate labeling [22]. Following the same standardization, a serious adverse device event (SADE) is defined as an adverse device event (ADE) that has resulted in any of the consequences characteristic for a SADE, with an unexpected SADE (USADE) being defined as a SADE that by its nature, incidence, severity, or outcome has not been identified in the current risk assessment. SADE and USADE will immediately be analyzed by the sponsor regarding possible root cause and possibility of reoccurrence. In addition, all statutory reporting duties will be fulfilled. In the case of USADE, the investigator has the same notification duties and reporting timelines as for SADE.

### Analysis and Statistical Methods

Descriptive statistics and patient data listings will be used to summarize the data. Continuous variables will be summarized by nonmissing values (n), mean and SD (in case of normal distribution), median, 25th and 75th percentiles (in case of nonnormal distribution), and minimum and maximum. Categorical variables will be summarized by frequencies and percentages. Stratification of descriptive categories within treatment groups may occur if such elaborations are thought to be useful. Inferential statistical tests may be used, as appropriate, with an α critical value of .05 to indicate statistical significance. Inferential statistical tests will be 2-sided, unless specified otherwise. Also, 95% CIs may be used to compare event rates to a historical and clinically meaningful standard or to investigate the course of biomarkers (or certain laboratory values) after CytoSorb therapy. Multivariate analysis may be used to determine independent predictors of study outcomes. Missing data is unavoidable for critically ill patients treated in the intensive care unit (ICU). The principle of analyses is to only include the nonmissing observations. For inflammatory biomarkers or laboratory values that are highly associated with the use of hemoadsorption devices, sensitivity analyses will be performed by applying a multiple imputation method under the missing-at-random assumption.

Unless specified otherwise, minimum and maximum will be displayed to the same level of precision as the observed value. Mean and median will be displayed to 1 level of precision greater than the observed value. The SD and SE will be displayed to 2 levels of precision greater than the observed value. All *P* values will be rounded to and displayed as 3 decimals. If a *P* value less than .001 occurs, it will be shown in tables as <.001.

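### The nonmissing-only rule has no exception for 90-day mortality, so a complete-case percentage would probably overstate it

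*Protocol article*

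**What the plan says.** Under Analysis and Statistical Methods, the article gives a single missing-data principle: "The principle of analyses is to only include the nonmissing observations". The one departure it names is that "sensitivity analyses will be performed by applying a multiple imputation method under the missing-at-random assumption", and that sentence is confined to inflammatory biomarkers and laboratory values. The same section summarises categorical variables as counts and percentages, and allows event rates to be set against a historical benchmark with 95% confidence intervals.

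Under Data Capture and Outcomes, the sources of vital status differ by stage of care. For the hospital stay, "Data collection is performed based on medical chart review and transcription of deidentified data collected from hospital admission through discharge". After that, the only prescribed contact is "a follow-up telephone call at 90 days (plus an additional 20 days if needed for administerial reasons) after the start of CytoSorb treatment". The listed time points carry a general caveat: "Data from the following time points will be collected if available". Textbox 3 lists ICU and in-hospital mortality, 90-day mortality with cause of death, and, at study exit, "vital status and registry exit date".

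Under Ethical Considerations: "A full data readout is performed at least annually". Enrolment continues meanwhile. Results reports 199 patients between July 15, 2022 and August 1, 2024, and projects about 300 a year, up to 3000 in 10 years.

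**The concern.** Whether day-90 status is missing depends on the outcome. A death in hospital is known without any call. So is survival for someone still in hospital at day 90. A patient discharged alive earlier normally enters the analysis only when the call gives an answer. If unknowns are dropped, the patients lost have nearly all survived their hospital stay, while all in-hospital deaths remain. The denominator shrinks on one side only.

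A related effect could arise at interim readouts. Read literally, the rule would count a recently enrolled patient who has died as a nonmissing event, and treat one who is alive but not yet at day 90 as missing.

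Mortality is among the key outcomes. A bias that varies with call success and cut date would make successive readouts hard to compare, and would distort any comparison with a benchmark. The part due to unreached patients does not shrink as the registry grows.

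**Working it through.** **Inputs.** From the article: the nonmissing-only rule, the sources of vital status, readouts at least once a year, and the enrolment figures. Its only size projection reproduces (300 × 10 = 3000) but has no bearing on the argument. Mortality, share unreached and timing of death are not given, so they are assumed and shown as ranges.

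**1. Unreached patients.** Let *h* be hospital mortality, *p* the risk of death from discharge to day 90 in those reached, *p*ᵤ the same risk in the unreached, and *u* the share of discharged patients without day-90 status.

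- True rate = h + (1−h)[(1−u)p + u·pᵤ]
- Complete-case rate = [h + (1−h)(1−u)p] / [h + (1−h)(1−u)]

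Base case, h = 40%, p = pᵤ = 10%: the true rate is 0.40 + 0.60 × 0.10 = 46.0%.

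| u | Complete-case rate | Excess (points) |
|---|---|---|
| 10% | 0.454/0.94 = 48.3% | +2.3 |
| 20% | 0.448/0.88 = 50.9% | +4.9 |
| 30% | 0.442/0.82 = 53.9% | +7.9 |

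Over h = 30-50% and p = pᵤ = 5-10%, the excess is +2.0 to +2.5 points at u = 10%, +4.4 to +5.3 at 20%, and +7.2 to +8.4 at 30%.

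**2. When the direction reverses.** In the base case with u = 20%, the true rate is 0.448 + 0.12·pᵤ. Setting this equal to 0.509 gives pᵤ ≈ 51%, which is the complete-case rate itself and about five times the mortality in those reached. At pᵤ = 30% the true rate is 48.4% and the excess is +2.5 points. At pᵤ = 60% the true rate is 52.0% and the error is −1.1 points.

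**3. Patients not yet at day 90, if the rule is applied literally.** From July 15, 2022 to August 1, 2024 is 2.05 years, so 199/2.05 ≈ 97 patients a year. About 97 × 90/365.25 ≈ 24 of the 199 (12%) would be inside 90 days.

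With *N* patients, *k* of them inside 90 days, a true 90-day rate *m*, and *D* deaths already seen among the *k*, the literal rule gives [(N−k)m + D] / [(N−k) + D]. *D* is computed for uniform entry and exponentially declining death times, with time constant 10 to 40 days, truncated at 90 days. For m = 40%, N = 199, k = 24 and a time constant of 20 days, D ≈ 7.6 and the figure is (70 + 7.6)/(175 + 7.6) = 42.5%.

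| Readout | True rate | Literal rule |
|---|---|---|
| N = 199, k = 24 | 40% | 42.1-42.8% |
| N = 300 after one year at 300/year, k = 74 | 40% | 44.9-46.3% |
| N = 3000 at 300/year, k = 74 | 40% | about 40.5% |

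**4. Scale.** At a 40% rate the 95% confidence half-width, 1.96√(0.4 × 0.6/N), is 6.8 points at N = 199 and 1.8 points at N = 3000. The 4.9-point excess at 20% unreached lies within the first and well outside the second.

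**5. Alternatives.** These were simulated for the base case at u = 20% with 200,000 patients, assuming gamma-distributed hospital stays and post-discharge deaths spread evenly to day 90. The true rate was 46.0%.

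- Kaplan-Meier with the unreached censored at discharge gave 48.7%. That censoring is informative: those censored have just survived their hospital stay, but are represented by a risk set that still contains inpatients.
- Hospital mortality plus the share discharged alive times post-discharge mortality in those reached gave 46.0%.
- By direct arithmetic, the all-alive and all-dead bounds are 44.8% and 44.8% + 12.0% = 56.8%.

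**The case against.** The strongest reply is that the quoted sentence is a general principle, introduced by a remark about missing ICU data and followed by one on laboratory values. Responsibilities and Dissemination refers to a statistical analysis plan, which is not shown. That plan may restrict the day-90 denominator or use the exit date and vital status. This stands in part: nobody can say from the article that the registry will report a biased figure. But the rule is stated for analyses in general, and its one named departure leaves mortality out. The point concerns what is written, not a missing detail.

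Four stronger readings are tempting, and the article does not support them.

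- A reader might infer that the rule drops survivors. The unreached are patients discharged alive whose later status is unknown; some will have died.
- A reader might infer that about 12% of patients are inside 90 days at every cut. That share holds at N = 199. At N = 3000 it is 24/3000 = 0.8% at 97 a year, or 74/3000 = 2.5% at 300 a year. Nor does the article say that patients not yet due are treated as missing.
- A reader might infer that deaths on days 91 to 110 will count as 90-day deaths. That follows only if status at the call is used undated. The extra 20 days is described as administrative latitude, and the outcome is still named 90-day mortality.
- A reader might infer that a historical comparison is planned. The article only permits one. The analysis is mainly descriptive, and ICU and in-hospital mortality depend far less on the call.

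**Conclusion.** The point holds in a qualified form. As written, the rule makes a complete-case 90-day mortality percentage probably too high, because unknown status arises almost only in patients discharged alive. Under the assumed ranges, with equal mortality in reached and unreached patients, the excess is about +2 to +8 points for 10-30% unreached. It turns negative only if mortality in the unreached exceeds the complete-case rate, about 51% in the base case at 20% unreached. Literal use of the rule at an interim readout would, on its own, raise the figure by about 2 to 3 points at N = 199 and about 0.5 point at N = 3000.

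The mechanism comes from the article; the sizes do not, since it reports neither mortality nor follow-up success. With near-complete follow-up and a closed-window denominator the problem would be negligible. It deserves correction before a 90-day figure is published, but it does not undermine the registry or its in-hospital outcomes.

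**What to change.** State that 90-day mortality is exempt from the nonmissing-only rule, and define it as follows.

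- **Denominator.** At each readout, include all patients whose day-90 window has closed by the cut date, whether dead or alive.
- **Event.** Count death dated on or before day 90 from the start of CytoSorb treatment. Use the day 90-110 call only to establish status at day 90.
- **Unknown status.** Keep patients discharged alive with unknown status in the denominator. One simple estimate is in-hospital mortality plus the share discharged alive times post-discharge mortality in those reached. Weighting or imputation among discharged patients is an alternative. Do not rely on Kaplan-Meier with censoring at discharge.
- **Reporting.** Give the number with unknown status and the all-alive and all-dead bounds. The bounds matter because the simple estimate also assumes that unreached patients resemble the reached. In the base case at 20% unreached, if their mortality were 30%, it would read 46.0% against a true 48.4%.

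The cost is about a paragraph of analysis text and a little more analysis work. Vital status and exit date are already collected; the date of death must be available for those who die. The most recent patients are left out of each interim 90-day figure: with closure at day 110, about 97 × 110/365.25 ≈ 29 of 199. They enter at the next readout.
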